### Examine Cost-Effectiveness and Sustainability

The study team will collect information on: (1) time spent by study staff for training, supervision, and technical assistance of counselors; (2) time participants spent in a counseling session; and (3) costs associated with test counselor delivery of the intervention. Capital equipment cost (eg, computer) and facility cost (eg, rent, telephone) at the study sites that are attributable to our intervention will be obtained from each site’s accounting records. Capital equipment cost will be distributed over a 4-year period with a 3% discount rate. Cost items that are not directly divisible between participants will be spread across relevant individuals (eg, spreading capital equipment and facility cost across all participants tested at each agency). A flat rate covering the cost of CTR materials for each intervention group will be estimated. No costs associated with research data collection will be included. These components of cost will be summed over the 15-month study period for each participant to generate an estimated per person cost. Effectiveness will be measured by examining relevant substance use and HIV-related outcomes reported by each YMSMTG over the 15-month period. Incremental cost effectiveness ratio (ICER) across treatment arms will be defined as ΔC/ΔE, where ΔC denotes the estimated difference in mean cost per intervention and ΔE reflects the estimated difference in mean effectiveness between the intervention and control group. ICER indicates the additional costs associated with the intervention for each new HIV infection avoided. Nonparametric bootstrap resampling will be used to estimate the 95% CI of ICER [63]. Primary analysis will be performed on participants with complete data. Sensitivity analysis will be conducted by including all participants with multiple imputation for those with missing data.

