### Outcomes

The trial focuses on 3 sets of outcomes: engagement in HIV prevention and care services; AOD use; and sexual risk. The trial will also measure satisfaction with the intervention.

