#### Biomarkers for HIV Prevention and Care

In addition to self-reported behavioral measures, the study will also collect biomarkers to test for HIV and STIs. At the intervention visits, HIV testing will be performed as part of CTR. STI screening: For syphilis screening, participants will undergo a blood draw for subsequent unheated serum regain test and, for chlamydia and gonorrhea screening, participants will provide a urine sample and pharyngeal, rectal, and/or vaginal swab cultures. Hepatitis C will be assessed using the OraQuick rapid test. Although we expect prevalence of hepatitis C to be low in an AOD population that has low levels of injection drug use (and thus hepatitis C will not be a secondary outcome), we will include hepatitis C testing to assess prevalence in this population. Those who are asymptomatic and test positive will be referred by study staff to local health care providers for further evaluation and treatment. All other STI tests will be processed by the Michigan Department of Health and Human Services. As required by state law, all new positive STI results will be reported to the State Health Department for the purposes of disease surveillance. The requirement for reporting of confidential test results to the health department will be explained in the informed consent. Condoms and water-based lubricant will be provided to all participants. We will screen for STIs at the final study assessment.

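### The cost-effectiveness ratio is labelled as cost per HIV infection avoided, but its denominator is built from other, participant-reported outcomes

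*Protocol article*

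**What the plan says.** All the key statements stand in the protocol article, section Examine Cost-Effectiveness and Sustainability.

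- On effectiveness: "Effectiveness will be measured by examining relevant substance use and HIV-related outcomes reported by each YMSMTG over the 15-month period".
- On the denominator of ΔC/ΔE: "ΔE reflects the estimated difference in mean effectiveness between the intervention and control group".
- On the meaning of the ratio: "ICER indicates the additional costs associated with the intervention for each new HIV infection avoided".
- On uncertainty: "Nonparametric bootstrap resampling will be used to estimate the 95% CI of ICER".

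The Outcomes section lists what the trial measures: "The trial focuses on 3 sets of outcomes: engagement in HIV prevention and care services; AOD use; and sexual risk".

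On HIV testing by the study, Biomarkers for HIV Prevention and Care says: "At the intervention visits, HIV testing will be performed as part of CTR". For the end of the trial the same section names only other infections: "We will screen for STIs at the final study assessment". Between surveys, the section Engagement in HIV Prevention and Care Services records a test result only for participants who tested.

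**The concern.** A ratio of costs to effects takes its unit from the denominator. If ΔE is a difference in testing, engagement or substance use, then ΔC/ΔE is a cost per unit of that outcome. It becomes a cost per infection avoided only if ΔE counts infections or a model links the two, and the article provides neither.

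At stake is how the ratio would be read. The Discussion presents the programme partly as a response to shrinking prevention funds. A funder who sees a cost per infection avoided will compare it with other such figures, although the number measures something else.

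A second question is whether the label could be made true by counting infections, and whether an interval for the ratio would then behave. That branch needs figures the article does not give, so it is worked below under stated assumptions.

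**Working it through.** **Step 1. The statements side by side (no outside figure needed).** The effect measure is participant-reported substance use and HIV-related outcomes. The denominator is the between-group difference in its mean. The stated unit is infections avoided. The three outcome sets are engagement, alcohol and drug use, and sexual risk. Infection is not named in any of them, and no conversion is described. The unit does not follow from the measure.

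**Step 2. What the trial was sized for.** Sample Size and Power gives 500 participants for a 20-point difference and 228 for a 30-point difference. It does not state the control rate. With α = 0.05/3, 80% power and

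n = [z(1−α/2)·√(2p̄(1−p̄)) + z(0.80)·√(p₁(1−p₁)+p₂(1−p₂))]² / (p₁−p₂)²,

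a control rate of 30% gives n = 124.3 for 30% vs 50%, so 125 × 4 = 500. For 30% vs 60% it gives n = 56.2, so 57 × 4 = 228. Both figures reproduce, so the size rests on engagement, with an inferred 30% base.

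**Step 3. If ΔE were infections.** Inputs from the article: 600 allocated 1:1:1:1, so 150 per arm; 20% loss leaves 150 × 0.8 = 120; the costing period is 15 months = 1.25 years. Assumed: an incidence of 1-4 per 100 person-years, with 10 as a stress case. Risk = 1 − exp(−rate × 1.25). With C and T the infections in the control and SUBI arms, P(ΔE ≤ 0) = Σ P(C = k)·P(T ≥ k), by exact binomial calculation at 150 per arm:

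| Rate per 100 person-years | Control risk | Control infections | P(ΔE ≤ 0), true 30% reduction | P(ΔE = 0), true 30% reduction | P(ΔE ≤ 0), true halving |
|---|---|---|---|---|---|
| 1 | 0.0124 | 1.9 | 50% | 23% | 41% |
| 2 | 0.0247 | 3.7 | 41% | 15% | 28% |
| 4 | 0.0488 | 7.3 | 32% | 10% | 17% |
| 10 | 0.1175 | 17.6 | 19% | 5% | 5% |

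At 120 per arm and rates of 1-4, P(ΔE ≤ 0) runs from 53% down to 35% (30% reduction) and from 45% down to 20% (halving). These are shares of simulated or enumerated trials, not of bootstrap resamples. A separate simulation of the bootstrap itself, with a true halving, rates of 1-5 and 120-150 per arm, gave a 95% interval for ΔE that included zero in about 79-98% of trials. About 6-32% of resamples had ΔE exactly zero, where the ratio is undefined.

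**Step 4. Detection after visit 2.** Suppose there is no true effect. Infections in the first 0.25 years are found alike in all arms at visit 2. In the following 1.0 year they are found in 30% of control and 50% of SUBI participants, which is the design difference on the inferred base. Detected infections then stand in the ratio (0.25 + 0.50 × 1)/(0.25 + 0.30 × 1) = 0.75/0.55 = 1.36. Conversely, a true rate ratio of about 0.55/0.75 = 0.73, a 27% reduction, would look like no difference.

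**Step 5. The same check with engagement as ΔE.** With 30% engaged in control, P(ΔE ≤ 0) at 150 and at 120 per arm is:

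- 20-point effect: 0.02% and 0.09%
- 10-point effect: 4% and 6%
- 5-point effect: 19% and 22%

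**The case against.** The strongest reply is that the article never says ΔE counts infections. A reader might infer from the infection wording that the whole ratio and its interval are uninterpretable because infections are too few and unequally detected. The documents do not support that as a flat statement. Sparse events and detection bias apply only if the HIV-related outcomes mean infections, and every percentage in Step 3 rests on an assumed incidence. Unequal detection is also an inference: both session types include an HIV test at visits 1 and 2, so bias can arise only afterwards and only if SUBI changes testing. This reply stands, and it is why those calculations are offered only to show that the alternative reading gives no rescue.

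Second, at the 20-point design effect an engagement-based denominator stays well away from zero, so a bootstrap interval for the ratio is workable. That stands too. It weakens at 5-10 points and fails near a null effect. Planning of this kind is often left to a fuller document, and nothing in the article rules out other displays.

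Third, the Trial Design section asks about costs only if SUBI is effective, and it asks about delivery costs. Per-person cost and ΔC come from staff time, session time and accounting records, which the label does not touch. This limits the consequence to the ratio.

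What the reply does not remove is the sentence itself. A full protocol could contain a conversion model, but the article states both the measure and the unit, and they do not match.

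**Conclusion.** The mismatch between effect measure and stated unit is wrong as written and depends on no assumption. Redefining the effect as infections would not mend it: with 2-7 expected control infections, the sign of ΔE would be wrong or null in about 32-50% of trials under a true 30% reduction. Those figures assume 1-4 infections per 100 person-years and 150 per arm. After visit 2, ascertainment would also depend on the behaviour SUBI is meant to raise.

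The concern about an interval for the ratio is real but conditional: minor at the design effect on engagement, material for small or null effects. There ΔC/ΔE passes through infinity, and a negative value can mean either cheaper and better or dearer and worse. The point merits correction, but it concerns a secondary ratio. The primary efficacy analysis and the comparison of delivery costs are unaffected.

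**What to change.** 1. Define ΔE as the difference between arms in the proportion meeting the primary engagement outcome, as that outcome is analysed in the Statistical Analysis section, and report the ratio as cost per additional participant engaged.
2. Delete the phrase that reads the ratio per infection avoided. Alternatively, confine it to a scenario labelled as modelling, with the conversion from measured outcomes to infections and its assumed incidence stated.
3. Keep the bootstrap, but also show its output as a cost-effectiveness plane, or as incremental net benefit with an acceptability curve, so that the result stays readable if ΔE is near zero.

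No new data are needed: items 1 and 2 are wording, and item 3 re-expresses the same resamples. The small cost is that net benefit and the acceptability curve require a willingness-to-pay range per additional participant engaged, to be stated in advance.

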### Trial Design

The research activities involve a 4-arm factorial RCT of approximately 600 AOD-using YMSMTG aged 15-29 years in the DMA. We will follow participants for 18 months, with follow-up assessments collected every 3 months.

The intervention comprises 2 visits separated by 3 months. Participants are randomized to receive either CTR (control) or a SUBI-adapted version of CTR (referred to as SUBI; intervention) in each visit. To examine how the sequencing and dosing of interventions impacts efficacy, we randomize at baseline into a factorial RCT. The control arm will receive CTR-only at both study visits 1 and 2. Experimental arm 1 (CTR+SUBI) will receive CTR at visit 1 and SUBI at visit 2. Experimental arm 2 (SUBI+CTR) will receive SUBI at visit 1 and CTR at visit 2. Experimental arm 3 (SUBI+SUBI) will receive the intervention condition at visits 1 and 2. Individuals who test HIV-positive at study visits 1 or 2 will receive case management and linkage to care, as offered routinely by each ASO where study activities take place.

This 4-arm factorial randomized design will help answer 3 important questions: (1) what is the impact of adapting current CTR to include SUBI on HIV engagement in care and sexual- and substance-related risk-taking behaviors among high-risk YMSMTG; (2) what combination of services (CTR-only, CTR+SUBI, SUBI+CTR, SUBI+SUBI) has the greatest impact on engagement in HIV prevention (where engagement in care is defined as routine HIV testing for seronegative YMSMTG and linkage and retention in care for seropositive YMSMTG); and (3) if effective, what are the costs of delivering SUBI compared with those of delivering CTR?

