### Sample Size and Power

The primary outcome for the proposed trial is successful engagement in care. For those who test seronegative at baseline, we define engagement in care as participation in routine HIV testing. For those who test seropositive at baseline, we define engagement in HIV care as linkage and retention in HIV care (per the Institute of Medicine guidelines of linkage within 30 days of diagnosis and at least 2 physician visits with a CD4 and viral load test in 12 months) and achievement of viral suppression. We define power as correctly identifying the difference in the proportions of YMSM with serospecific engagement in HIV care within 15 months of each active treatment condition (3 arms: SUBI-CTR, SUBI-SUBI, CTR-SUBI) to the control arm (CTR-CTR), thus powering for 3 independent hypothesis tests. Our sample size calculations are based on a 2-sample test of proportions using a 2-sided significance level of *P*<.05 altered by the number of comparisons using a Bonferroni adjustment (significance level is *P*=.02 for 3 comparisons). To have 80% power to compare each active treatment to the control group in a 4-arm trial, we require at least 500 participants to find a 20% difference between each treatment and control and 228 participants to find a 30% difference. To allow for 20% loss to follow-up (our previous trials have each achieved retention rates of >90%), we estimate a sample of 600 YMSMTG to be enrolled.

Participants may continue the study even if they miss follow-ups or visits intermittently over the data collection period. We will compare those who completed different follow-up interviews with those who did not on key predictors from the baseline assessment to check for possible sampling bias due to missing data. Missing data will be minimized by the computer-based entry for all measures. The use of Expectation-Maximization algorithm and multiple imputation approach in longitudinal analyses will help overcome missing data concerns when appropriate.

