#### Engagement in HIV Prevention and Care Services

We will ask YMSMTG having unknown or negative HIV status to indicate the date of any recent HIV and STI tests. At baseline, we will ask participants to note if they have ever been medically diagnosed as having one or more STIs. Among those diagnosed, we will ask if the STI diagnosis occurred in the prior 12 months. In follow-up surveys, we will ask participants to report if they tested for STIs in the prior 3 months and whether any of their tests were reactive.

At each follow-up session (visits 3-7), we will measure the primary outcome of repeat HIV testing. For anyone who tested in each intersurvey period, we will assess the test result and motivations for testing (exposure-related vs regular health checking). For seropositives, the survey will assess the incidence of HIV-related physician visits, including whether CD4 counts and viral load tests were conducted and prescriptions for antiretroviral therapy (ART) were given. We will also ask participants to self-report their adherence to ART using an abbreviated 6-item questionnaire based on the AIDS Clinical Trial Group assessment. Participants are asked to note, using a scale ranging from “never” to “often,” if they missed their HIV medication over the past month for one of the listed reasons. Seropositives will also provide a blood sample for a viral load test. Viral load testing will be done every 6 months. We prioritize viral load tests over a biomarker of adherence, given that adherence is the primary pathway to viral suppression.

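### The primary cost-effectiveness ratio uses only participants with complete data; the already planned imputation of all randomized participants should be the primary analysis instead

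*Protocol article*

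**What the plan says.** The section Examine Cost-Effectiveness and Sustainability ranks the two analyses explicitly: "Primary analysis will be performed on participants with complete data", and then "Sensitivity analysis will be conducted by including all participants with multiple imputation for those with missing data".

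The same section defines the effect side: "Effectiveness will be measured by examining relevant substance use and HIV-related outcomes reported by each YMSMTG over the 15-month period". The cost side is built from staff time, session time, counselor delivery costs, site accounting records and a flat rate for materials. Research data-collection costs are excluded.

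Sample Size and Power expects gaps: "Participants may continue the study even if they miss follow-ups or visits intermittently over the data collection period". It allows for 20% loss and reports retention above 90% in the team's previous trials. It also plans a baseline comparison of those who did and did not complete follow-up interviews, and foresees the EM algorithm and multiple imputation in the longitudinal analyses.

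No section says what counts as complete data for the ICER, or what share of participants is expected to have it.

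**The concern.** Having complete data is settled after assignment. It depends on whether a participant keeps reporting over 15 months. The mean differences in cost and effect that form the primary ICER would therefore describe a subset selected after randomization.

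The trial's own rationale makes informative gaps plausible. The Abstract presents substance use as a barrier to HIV prevention and care services, everyone enrolled uses substances, and the intervention is meant to change both substance use and engagement. Continued follow-up could be related to arm and to outcome at once.

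The cost of delivering SUBI compared with CTR is one of the three questions listed in Trial Design, so the primary ICER is its headline answer. If the two analyses disagree, the plan gives priority to the one that ignores what is known about the incomplete participants.

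**Working it through.** **Inputs**
- Planned enrolment: "we estimate a sample of 600 YMSMTG to be enrolled" (Sample Size and Power).
- Loss allowance 20%; previous retention above 90% (same section).
- Schedule: "We will follow participants for 18 months, with follow-up assessments collected every 3 months" (Trial Design).
- Follow-up occasions: "At each follow-up session (visits 3-7), we will measure the primary outcome of repeat HIV testing", that is 5 after the two intervention visits. The Incentives section agrees: 2 × $25 + 5 × $30 = $200.

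**1. The plan's own figure.** The enrolment target is the required 500 raised by 20%: 500 × 1.20 = 600. No sample size or complete-data share is stated for the ICER, so the exclusion has to be worked out from the 600.

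**2. Exclusion from dropout alone**
- At the plan's allowance: 600 × 0.20 = 120 left out, 480 analyzed.
- At 90% retention: 600 × 0.10 = 60 left out, 540 analyzed. Earlier trials did better than 90%, so 60 is an upper figure for that scenario.

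**3. Exclusion if every wave were required.** This step rests on assumptions that are not in the article: complete data means all k occasions, and misses are independent with completion r at each. The complete share is then r^k. I take k = 5 (visits 3 to 7), and k = 6 if visit 2 is also counted.

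| r | k = 5 | k = 6 |
|---|---|---|
| 0.98 | 0.904 (542 of 600) | 0.886 (532) |
| 0.95 | 0.774 (464) | 0.735 (441) |
| 0.90 | 0.590 (354) | 0.531 (319) |

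Independence spreads the misses over more people than clustered dropout would, so for a given r these shares lean low.

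**4. How selection enters the ICER.** In arm a, let π_a be the share with complete data and g_a the mean effect in completers minus that in non-completers. The complete-case mean differs from the mean of all randomized by (1 − π_a) × g_a. For active arm A and control C, the error in the effect difference is

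(1 − π_A) g_A − (1 − π_C) g_C.

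- Equal loss of 20% in both arms: 0.20 × (g_A − g_C). At 10% loss: 0.10 × (g_A − g_C).
- Equal gap g in both arms: (π_C − π_A) × g.
- Equal loss and equal gap: zero.

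The same expression applies to the cost difference. If the error in the effect difference is e, the ICER is multiplied by ΔE/(ΔE + e), so a small ΔE makes the ratio sensitive. The article gives no value for the gaps, so neither the size nor the direction of bias can be stated.

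**5. Data set aside.** None of the listed cost components is described as a survey item. Someone who attends sessions and then misses surveys still has a delivery cost that records can supply. A complete-case rule drops that cost together with any effectiveness data the person did report.

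**The case against.** The strongest reply is that the problem is already contained. The all-participant imputation is prespecified, completers will be compared with non-completers at baseline, and the cost question is conditional on the intervention being effective. All arms have two visits of about 30 minutes and the same incentives, so differential missingness is possible but not shown. This stands as a limit on severity. It does not justify the ranking, because the complete-case ICER remains the headline result.

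Three stronger readings are tempting, and the documents do not support them.
- *A large share, perhaps half, of the sample is discarded.* The documented figures give about 10% to 20%. The larger losses in step 3 need every wave to be required and independent misses, and the article states neither. Participants are asked for dates of recent HIV tests, so a skipped wave may be recoverable for some outcomes.
- *One missed survey makes both cost and effect missing.* Costs come from study and site records, and the article does not say that effects are summed over waves.
- *Complete-case analysis is valid only if data are missing completely at random.* Step 4 shows that a between-arm difference can remain unbiased under weaker conditions, for example when loss and the completer gap are the same in each arm.

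**Conclusion.** The point holds as a matter of ranking. The primary ICER is conditioned on attendance after randomization, so it is not a comparison of the groups as assigned. It can be biased if missingness is related to arm and outcome, and it discards recorded costs and partial outcomes. The documented size is about 120 of 600 excluded at the 20% allowance and about 60 at 90% retention. A larger exclusion depends on the undefined meaning of complete data and on how common intermittent gaps turn out to be.

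Imputation is not assumption-free: it relies on missingness being explained by the variables in the imputation model. It does keep everyone randomized and use what was observed. The point is confined to the cost-effectiveness analysis; the primary efficacy analysis is untouched.

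**What to change.** Swap the two analyses in Examine Cost-Effectiveness and Sustainability.
- **Primary:** all randomized participants as assigned, with missing effectiveness outcomes imputed by arm. Take delivery costs from records, so that an undelivered session carries no delivery cost. Combine the imputation with the planned bootstrap for the confidence interval.
- **Sensitivity:** complete cases, with a statement of what complete data means.

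Both analyses are already planned, so the cost is a revised paragraph and a little extra work to combine imputation with the bootstrap. No further data collection is needed. The change should be fixed before outcome data are examined; the Results section reports 142 participants randomized as of February 22, 2018.
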